Although these figures are encouraging, it should be noted that these studies all trained their classifiers on relatively small datasets of 20-30 individuals per group, and none of them tested the performance of the models on a second replication dataset; hence, the reliability and generalizability of this approach remains unproven. One of the few studies to use a large training set (n=238) as well as replication datasets achieved 91% accuracy in classifying rs-fMRI scans as belonging to either children age 7-11 or adults age 24-30, with 92% and 93% accuracy on 2 replication datasets of sizes n=195 and n=186, suggesting that good replicability can be achieved if the training set is sufficiently large.

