#### 1.4.0 Objectives and Hypotheses

In summary, TBS has been shown to be effective in open-label studies of major depression. It has also been shown to have greater potency than conventional protocols in studies of motor physiology. However, to date there has been no direct comparison of the relative efficacy of these different forms of rTMS for TRLLD under randomized controlled conditions. This study will address the question of the relative efficacy of conventional versus theta-burst stimulation in the setting of TRLLD by comparing conventional HFL rTMS to TBS, while training and validating classifier algorithms for predicting treatment response using rs-fMRI.

[figure not shown]

**Objective 1:** To compare the effectiveness of a course of 4 minute sessions of TBS to a course of 45 minute sessions of conventional rTMS in LLD.

**Hypothesis 1:** Sequential bilateral forms of TBS will have non-inferior effectiveness compared to sequential bilateral conventional rTMS in older adults with depression.

**Objective 2:** To determine if an automated classifier can use pre-treatment resting-state fMRI, clinical and cognitive data to predict treatment outcome for both TBS and conventional rTMS.

**Hypothesis 2:** Patterns from whole-brain functional connectivity, obtained from pre-treatment rs-fMRI, will distinguish responders and nonresponders with >85% accuracy for TBS and standard rTMS.

**Exploratory Objective 1:** To compare network connectivity in depressed adults across the lifespan and rTMS-induced changes between bilateral and unilateral stimulation approaches using existing unilateral data in adults <60 from our group.

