## 2.0 Significance

If the study hypothesis is confirmed, the implication will be that rTMS can maintain or better its current levels of efficacy using treatment protocols that can be completed in 1/10 the time of the standard form of treatment. An 8-minute treatment protocol would allow for up to 40 patients to be treated per rTMS device per day, and with a 4 week treatment protocol this would imply a capacity of nearly 500 patients per device per year. The cost of rTMS per patient could also be reduced proportionately.

In future treatment, a reliable pre-treatment fMRI test could spare non-responders from futile treatment while offering a recommendation for patients with favorable network activity patterns on fMRI. If fully implemented, this would boost the percentage of successful outcomes to 90% response and 60% remission *among treated patients*. In health-economics terms, this would reduce the cost per response. Given that responder and remitter patients would be more likely to return to work and less likely to require long-term disability support, rTMS could potentially have a positive impact on both the overall rates of treatment-resistant depression and on the significant social, economic, and health costs of the disease itself.

Our proposed trial will be large enough to demonstrate non-inferiority of TBS compared to standard rTMS, while training and validating classifier algorithms for predicting treatment response using rs-fMRI. These objectives, if realized, would yield a direct and near-term payoff in terms of outcomes and socioeconomic burden for the growing number of older adults with depression.

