### 3.2.3 Outcome Analysis

**Objective#1:** Assessing non-inferiority of bilateral TBS based on change on the MADRS, an ANCOVA covarying for baseline differences will be used to measure the change at the final time point for each subject. This will be the primary clinical outcome measure.

Secondary outcome measures will include change from baseline to endpoint on the HDRS-17 and response and remission on the HDRS-17 and MADRS.

For categorical outcome measures, response will be defined as  $\geq 50\%$  reduction in symptoms on the HDRS-17. Remission will be defined as a HDRS-17  $\leq 10$  and a MADRS  $\leq 10$  at the week 4 or 6 final time point. Other secondary outcome measures will explore comparison of side effects between the two treatment arms, anxiety scales, quality of life scales and cognitive measures.

**Objective#2:** Outcome prediction from whole-brain rs-fMRI scans, data will be analysed using the FSL platform and in-house scripts to extract whole-brain regional connectivity matrices, followed by automated classifier training, using a support vector machine approach according to previously reported methodology. Based on preliminary data, classifiers will be trained on 4 features: whole-brain functional connectivity, region-wise betweenness centrality, and edge-wise functional connectivity variability. Automated classifiers will be trained and tested on the datasets for standard bilateral groups, with iterative cross-validation to ensure generalizability.

[figure not shown]

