## Automated Classifier Construction

Training, testing, and cross-validation of automated classifiers will follow methods previously described for disease state classification using support vector machines (SVM). First, for each feature within the a given map, the Kendall tau rank correlation coefficient will be calculated as a non-parametric measure of the feature's relevance in discriminating responders from nonresponders. Next, features will be ranked according to discriminative power (i.e., absolute value of tau). Next, a leave-one-out cross validation approach will be used, omitting one subject per iteration during classifier training. Next, the set of consensus features (showing significant discriminative power across all 200 iterations) will be identified. This set of features will be used for construction and performance evaluation of the SVM. Classifier performance will be evaluated both in terms of overall accuracy and negative predictive value. The probability of obtaining the calculated performance under the null hypothesis will be determined using permutation testing, in which the class labels of the training data are randomly permuted and the training and cross-validation repeated, over 10 000 iterations, as previously described. SVM performance in discriminating responders from non-responders will be assessed by this method on each of the 4 feature sets described above. The performance of each classifier will be compared using the area-under-the-curve of the receiver-operating characteristic, chi-squared tests on overall accuracy and negative predictive value, and the decision-analytical approach of Vickers, which accommodates a spectrum of thresholds for pursuing or foregoing treatment.

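### Leave-one-out within the trial's own sample is said to ensure generalizability, but by the protocol's own account it gives internal validation only

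*Protocol*

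**What the plan says.** Protocol section 1.3.0 reviews earlier imaging classifiers. It notes training sets of 20 to 30 people per group and adds that "none of them tested the performance of the models on a second replication dataset; hence, the reliability and generalizability of this approach remains unproven". Its favourable example trained on 238 scans and was then scored "with 92% and 93% accuracy on 2 replication datasets of sizes n=195 and n=186", from which it draws the lesson "suggesting that good replicability can be achieved if the training set is sufficiently large".

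Hypothesis 2 (section 1.4.0) is that baseline connectivity patterns "will distinguish responders and nonresponders with >85% accuracy for TBS and standard rTMS". Section 2.0 says the trial will be large enough to show non-inferiority "while training and validating classifier algorithms for predicting treatment response using rs-fMRI"; section 1.4.0 uses the same description.

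Under Objective 2, section 3.2.3 (Outcome Analysis) says the classifiers will be trained and tested "with iterative cross-validation to ensure generalizability". The section on Automated Classifier Construction gives the method: "a leave-one-out cross validation approach will be used, omitting one subject per iteration during classifier training", followed by a permutation test of the class labels. The protocol names no second cohort, hold-out set or external dataset for the classifier. The existing data on adults under 60 belong to Exploratory Objective 1, a comparison of network connectivity, and are not assigned to classifier testing.

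**The concern.** The protocol applies two standards to the same property. When it judges earlier work, the lack of a second dataset leaves generalizability unproven. When it describes its own work, cross-validation inside one dataset is said to secure it. The method is also taken from one of the studies it criticises: reference 60, the whole-brain connectivity classifier of depression, is among those discussed in section 1.3.0 and is cited in section 3.2.3 and in Automated Classifier Construction as the methodology to follow.

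This matters because of the use foreseen in section 2.0, a pre-treatment scan that would steer predicted non-responders away from treatment. A reader who takes the wording at face value could treat a classifier that passes 85% by leave-one-out as ready for other clinics, when it has been checked only on patients from this trial.

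**Working it through.** The main check sets passages side by side; a few figures fix the scale.

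**1. Sample available to the classifier.** Section 3.2.1 gives a margin of 2.75, an SD of change of 7.8, significance 0.05 and power 80%. At one-sided 0.05:

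n per arm = 2 × (1.645 + 0.842)² × 7.8² / 2.75² ≈ 2 × 6.183 × 60.84 / 7.5625 ≈ 99.5, so 100 per arm and 200 in total.

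This reproduces the stated figure; one-sided 0.025 would give 127 per arm. Automated Classifier Construction refers to features "the set of consensus features (showing significant discriminative power across all 200 iterations) will be identified". With one iteration per omitted subject, 200 iterations take up the whole planned sample, so no block of patients remains for a separate test.

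**2. Standard against plan.**

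| Section 1.3.0 on earlier work | This trial | Answered? |
|---|---|---|
| Small training sets, 20 to 30 per group | About 200 patients; about 100 per arm if the two treatments are modelled separately, as Hypothesis 2 can be read | Largely |
| No test on a second dataset | Leave-one-out and permutation on the same patients | No |

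**3. What each check can show.** Leave-one-out scores each patient with a model trained on the others. Done properly, it estimates accuracy for further patients drawn as these were: same sites, procedures and period. Permutation asks whether the association in this sample exceeds chance. Neither uses data from outside the trial.

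**4. Precision of a cross-site test.** Section 3.1.4 stratifies randomization by the two sites, so site is recorded. Site sizes are not given, so they are assumed here. At a true accuracy of 85%, the approximate 95% half-width is 1.96 × √(0.85 × 0.15 / n):

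| Patients tested | Half-width (percentage points) |
|---|---|
| 25 | 14.0 |
| 50 | 9.9 |
| 100 | 7.0 |
| 200 (all, leave-one-out) | 4.9 |

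**The case against.** **Sample size.** Section 1.3.0 makes two criticisms, and its closing sentence links replicability to a large training set. Section 3.2.1 says this database will exceed any earlier one in late-life depression. That is a real improvement and answers the first criticism. It does not answer the second, because the large-sample example could speak of replicability only by scoring two further datasets.

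**Usage and timing.** Validating can loosely include cross-validation, the clinical use in section 2.0 is conditional, and a statistical analysis plan not seen here could add an external test. All fair. But the point is not that something is missing: the protocol states a method and credits it with a property that method does not have. That wording needs correcting whatever the analysis plan adds.

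**Stronger readings that the documents do not support.**

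- A reader might infer that a site or scanner signature could by itself produce a positive result. Suppose response were 60% at one of two equal sites and 40% at the other, with site perfectly readable from the scan. Site alone would then give (0.60 + 0.60)/2 = 60% accuracy. The binomial chance of exceeding 85% from there is about 3 × 10⁻¹⁵ with 200 patients and about 10⁻⁸ with 100. The protocol gives no response rates by site and does not say where patients are scanned, so the example shows neither size nor likelihood.
- A reader might infer that leave-one-out itself inflates accuracy, or that no patient is ever held out. Each scored patient is omitted from training in that iteration. In a small simulation with pure-noise features and selection redone inside every fold, leave-one-out gave 43% to 54% against a true 50%, so no inflation. Using the consensus features for both building and scoring is a separate matter and is not relied on here.

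**Conclusion.** The point holds as a mismatch between what the protocol claims and what its design can show. Leave-one-out plus permutation on about 200 trial patients is a legitimate internal estimate, and by the reasoning of section 1.3.0 it leaves generalizability unproven. Meeting the >85% threshold this way would be an internal result.

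No numerical bias is claimed. How much accuracy would fall elsewhere cannot be derived from the document. The conclusion rests only on the protocol's wording and on no separate classifier dataset being named in it. It concerns Objective 2, one of the two main objectives; the MADRS non-inferiority analysis does not depend on it.

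**What to change.** 1. In sections 1.4.0, 2.0 and 3.2.3 (Outcome Analysis), replace the claims of ensured generalizability and of validating with *internal (cross-)validation*.
2. Beside Hypothesis 2, state that reaching the >85% threshold by leave-one-out is an internal result pending replication in a separate dataset.
3. Add a sensitivity run that trains at one site and tests at the other, using the site already recorded for stratification. Report its accuracy and confidence interval next to the leave-one-out figure. Both sites belong to the same trial, so this informs the question but does not replace replication.

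The cost is a wording change and a little extra analysis; no patients are lost from training the main classifier. The downside is imprecision if one site is small, which is possible because section 3.1.3 names only one institution's clinics, together with clinician referrals, as sources of patients.

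A locked hold-out by enrolment date, or training on one arm and testing on the other, are optional design choices and not required corrections. With a quarter set aside, the hold-out would cut training from about 200 to about 150 patients and still come from the same sites. Poor transfer between arms could reflect predictors that truly differ by treatment.

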### 3.2.3 Neuroimaging Data Analysis: Preprocessing and Feature Construction

Functional neuroimaging data will be analyzed using FSL for standard preprocessing steps including tissue segmentation, motion correction, co-registration of functional to anatomical scans, and spatial normalization to the MNI-152 template brain. Resting-state activity analysis will employ the aCompCor method for removal of white matter and cerebrospinal fluid signal artifacts, and FSL for bandpass filtering of BOLD time-courses (0.009-0.09 Hz) followed by extraction of the signal time-course from a 9mm radius spherical region of interest (ROI) centred on the L and the R DLPFC stimulation coordinates [ $x \pm 38$   $y + 44$   $z + 26$ ]. This time course will be used to generate whole-brain voxelwise maps of functional connectivity to the L and R DLPFC seed ROIs in each subject.

Following our previously published methods for analyses of whole-brain connectivity as a predictor of rTMS outcome, we will apply a 516-region whole brain functional atlas to extract time-course of activity for each region, then calculate the correlation (Pearson's  $r$ ) of each time course to all other time-courses to create a whole-brain cross-correlation matrix for each subject, followed by application of LeDoit-Wolf shrinkage estimator and calculation of the partial correlation matrix among all regions, thus removing the effects of spurious correlations among regions due to spurious variance sources such as scanner noise or residual subject motion.

Next, this matrix will be used to construct a weighted, undirected graph of whole-brain functional connectivity. This graph will be used to calculate the normalized betweenness centrality (BC) for each brain region in each subject, using methods described in technical detail in our previously published work using this graph theoretical metric to predict rTMS treatment outcome in TRD.

Finally, the functional connectivity variability (FCV) will be calculated between each pair of regions in the 516-region atlas in each subject. FCV is a *dynamic* measure of functional connectivity, reflecting the stability of the correlation in activity between any two brain regions over the entire duration of the scan; a related approach is described in detail in Kucyi et al. 2013. To calculate FCV for a given pair of regions, a "sliding window" of data is established using the first 15 timepoints in each data series, and the Pearson's  $r$  correlation calculated for this window. The window is then advanced 1 timepoint, and the process repeated, until the window reaches the end of the 300-timepoint series. The result is a series of  $r$ -values reflecting the *evolving* functional connectivity between the two regions over time. The variance of this  $r$ -series is used as the FCV. We will also explore baseline FLAIR (to assess vascular burden) and diffusion tensor imaging (to assess white matter integrity) compared to healthy controls as vascular burden has been associated with depression in late-life.

In summary, the analysis methods will extract four kinds of feature maps for use in training automated classifiers for outcome prediction in each subject: i) a voxelwise map of correlation to the activity in the L and R DLPFC ROIs; ii) a whole-brain cross-correlation matrix of all 516 regions to one another; iii) BC values for each of the 516 regions; iv) FCV values for the cross-correlation of all 516 regions to one another over time.

[figure not shown]

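### The protocol's stated safeguard against residual head motion, partial correlation, covers betweenness centrality but bypasses two of the four classifier feature sets and is unclear for a third

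*Protocol*

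**What the plan says.** Protocol section 3.2.3, Neuroimaging Data Analysis, puts all functional data through FSL motion correction, aCompCor and band-pass filtering. Two branches follow.

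- **Seed branch.** The DLPFC time course is extracted, and "This time course will be used to generate whole-brain voxelwise maps of functional connectivity to the L and R DLPFC seed ROIs".
- **Regional branch.** Time courses from 516 regions give a Pearson matrix, then Ledoit-Wolf shrinkage, then "calculation of the partial correlation matrix among all regions". The protocol says this works by "thus removing the effects of spurious correlations among regions due to spurious variance sources such as scanner noise or residual subject motion".

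Betweenness centrality comes from the regional branch. On its source the section says only that "this matrix will be used to construct a weighted, undirected graph of whole-brain functional connectivity". FCV is the variance of Pearson's r over a sliding window that "is established using the first 15 timepoints in each data series" and advances one point at a time to the end of a 300-point series.

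The section's summary lists four feature sets. Set i is "a voxelwise map of correlation to the activity in the L and R DLPFC ROIs", set ii is "a whole-brain cross-correlation matrix of all 516 regions to one another", set iii is betweenness centrality, and set iv is "FCV values for the cross-correlation of all 516 regions to one another over time".

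Under Automated Classifier Construction, a support vector machine is assessed on each set, tested by permuting class labels, and the four classifiers are compared with one another.

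**The concern.** By speaking of residual motion, the protocol accepts that some motion signal survives realignment and aCompCor. It then gives partial correlation the task of removing it. A reader would take the imaging features to be protected, but the step lies on the path of only some of them.

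Motion is a property of the person scanned. If it differs between responders and non-responders, features that carry it will separate the two groups. The permutation test asks whether labels and features are associated, not why, so it would count a motion difference as a success. The four sets are also unequally exposed, so the comparison between classifiers could partly rank them by how much motion they carry. Set ii matters most, because section 3.1.1 makes whole-brain functional connectivity the primary neuroimaging outcome, and section 2.0 foresees a scan-based test that would steer patients away from treatment.

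**Working it through.** **Step 1. Trace each feature set (Protocol section 3.2.3, Neuroimaging Data Analysis).**

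| Set | Built from | Through partial correlation? |
|---|---|---|
| i, seed maps | DLPFC time course, before the regional matrix is described | No |
| ii, regional matrix | Called a cross-correlation matrix, the term the section uses before shrinkage and partialling | Unclear |
| iii, betweenness centrality | Graph of *this matrix*, most naturally the partial one | Yes |
| iv, FCV | Pearson's r in 15-point windows (300 − 15 + 1 = 286 windows) | No |

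Two of four bypass the step, possibly three. Section 3.2.3, Outcome Analysis, does not settle set ii: it announces four features and names three.

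**Step 2. Is *removing* right where the step applies?** With 300 timepoints the sample covariance of 516 regions has rank at most 299, so it is singular and can be inverted only after shrinkage. The partial correlations are therefore regularised estimates. They can reduce a shared signal, but nothing guarantees that they remove it.

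**Step 3. Illustration of direction, not of size.** The protocol states no figure to reproduce. A simulation used its 516 regions, 300 timepoints, 0.009–0.09 Hz band, Ledoit-Wolf shrinkage and 15-point windows, with 25 simulated subjects per setting. Assumed and not in the protocol: repetition time 2 s, 12 networks, five motion events per scan, and the residual motion shares below. One region served as the seed, and FCV was computed on 80 regions. True connectivity was held fixed, and the values are means over unrelated regions.

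| Residual motion, share of variance | 0% | 5% | 10% | 20% |
|---|---|---|---|---|
| Seed correlation | −0.005 | 0.051 | 0.083 | 0.208 |
| Pearson edge | 0.001 | 0.049 | 0.097 | 0.191 |
| FCV | 0.182 | 0.185 | 0.193 | 0.208 |
| Partial correlation | 0.0000 | 0.0002 | 0.0002 | 0.0002 |

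In units of the between-subject SD at zero motion, FCV moved by 2.0, 5.8 and 13.4 at 5%, 10% and 20%. Partial correlation stayed tiny in absolute size but still moved by 3.9, 4.6 and 5.4 of its very small SDs. Motion is strongly reduced there, not removed.

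A second simulation (40 regions, 300 timepoints, residual spikes of 1.5 to 3 signal SD) correlated motion across subjects with each measure: about 0.3 to 0.8 for Pearson connectivity, −0.25 to −0.57 for FCV and 0.16 to 0.29 for shrunken partial correlation. The sign for FCV is opposite to that in the first simulation, so it depends on the assumed motion model.

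**Step 4. What could motion alone achieve?** Assume motion is normal with equal variance, the two outcome groups are of equal size, and they differ by d SD. The best possible accuracy is Φ(d/2).

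- d = 0.4: Φ(0.20) = 0.579
- d = 0.5: Φ(0.25) = 0.599
- To reach 0.85: d = 2 × Φ⁻¹(0.85) = 2 × 1.036 = 2.07

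Chance of a one-sided p < 0.05 against 50%, for a classifier at that ceiling (exact binomial, treating predictions as independent):

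| Assumed d | n = 200 (113 or more correct) | n = 100, one arm (59 or more correct) |
|---|---|---|
| 0.2 | 26% | 18% |
| 0.4 | 69% | 46% |
| 0.5 | 85% | 61% |

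The normal approximation at n = 200 gives 73% and 88% for d = 0.4 and 0.5, slightly too high. All of these are upper bounds, because a real classifier would not sit at the ceiling.

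**The case against.** The strongest reply is that the text does not contradict itself: the sentence concerns correlations among regions and never claims to cover seed maps or FCV. Every feature set also gets motion correction and aCompCor. Both statements are true. What remains is that the only step credited with dealing with *residual* motion is not on the path of two sets, and the label of set ii leaves a third open.

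A reader might also infer more than the documents support:

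- **That the imaging results will reflect motion.** Nothing in the protocol shows how much motion survives or whether it differs by response, and the simulations assume the contamination.
- **That motion could confirm Hypothesis 2.** It could not plausibly do so. The target is over 85% accuracy, which would need a motion difference of about 2.07 SD.
- **That the protocol is at fault for lacking scan-exclusion or censoring thresholds.** Those may properly sit in a statistical analysis plan that is not shown.
- **That all imaging contrasts are equally exposed.** The lifespan comparison is exploratory, and the only patient-control imaging contrast spelled out uses FLAIR and diffusion imaging, not these feature sets.

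**Conclusion.** The point holds in limited form. The motion safeguard applies to set iii, does not apply to sets i and iv, and is undetermined for set ii. Even where it applies, *removing* overstates what a shrunken partial correlation does.

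The consequence is conditional: if residual motion differs between responders and non-responders, the uncovered features can carry it, and the permutation test would not separate that from a network effect. The size is unknown. Under assumed differences of 0.2 to 0.5 SD and an ideal motion-only classifier, accuracy would be at most 54% to 60%, with an 18% to 85% chance of nominal significance depending on d and on whether the arms are pooled. The realistic harm is a significant result misread as a network finding, some inflation of accuracy, or a distorted ranking of the four classifiers. This touches Objective 2 and the functional-connectivity comparisons only. The change is worth making because it is cheap and permutation cannot substitute for it.

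**What to change.** 1. State which matrix forms set ii: the partial-correlation matrix, if that is what is meant, or otherwise the one that is.
2. Restrict the motion statement to the features it covers, and say *reducing* in place of *removing*.
3. Compute mean framewise displacement per scan from the realignment parameters that motion correction already produces. Adjust every feature set for it inside each training fold, with the adjustment estimated on the training subjects only. Covary for it in any functional-connectivity comparison with controls or younger adults.
4. Report the accuracy of a classifier given motion alone, as the benchmark for the four imaging classifiers.

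Volume censoring should not be required for FCV. It would break the contiguous 15-point windows and force that measure to be redefined.

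The cost is a little more analysis and no new data. The downside is that adjustment may remove some true signal that happens to correlate with motion.
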